#### Post study treatment follow-up phone call

This phone call will be planned 1-month after the “End of study treatment visit”.

The following will be performed during the post-treatment phone call:Neuropathic pain assessment: 11-point NRS, and if the pain score ≥ 4 / 10 then the perform DN4 interview and complete the NPSI questionnaire if the DN4 interview positive (score ≥ 3 / 7),Completion of study questionnaires (QLQ-CIPN20),Assessment of painkiller consumption (if applicable),Evaluation of safety (adverse effects by NCI CTCAE v4.0).All the questionnaires will be given to the patients during V4 to allow them to complete the questionnaires at home after 1-month. The phone call will remind the patients to return the completed questionnaires to the investigating centre.

### Statistical considerations

#### Sample size estimation

Fleming’s one-stage design will be used for sample size estimation. Sixty-six evaluable patients (33 by arm) will be accrued. The null hypothesis that the responder rate is 10% (maximal non-efficacy threshold, according to Smith et al*.* [43]) will be assessed against a one-sided alternative for the donepezil arm. The null hypothesis will be rejected if 7 assessable or more responders are observed in the 33 patients of the donepezil arm. This design yields a type I error rate of 0.0417 and a power of 91% for a responder rate of at least 30% in the donepezil arm (minimal clinical efficacy threshold). Thus, we have decided to include a total of 80 patients (2 × 40) to take into account lost to follow-up (20%, according to clinical practice with Alzheimer patients, which mainly corresponds to a poor tolerance at 5 mg/day dosage or when switching from 5 mg/day to 10 mg/day dosage), and possible tumor recurrence.

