## Methods / design

### Study design

The present study is a randomised, triple-blinded (patients, clinicians and pharmacists), and multicentre proof-of-concept trial that assesses the efficacy and safety of donepezil in patients with OIPN. The plan is to include 80 patients from 26 cancer centres and hospitals in France. The duration of the study is 20 weeks for the patients, including 4 weeks for treatment initiation, 12 weeks of stable treatment and 4 weeks of follow-up.

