Because of the absence of preliminary clinical results in the literature about donepezil and CIPN, and the recommendations of international experts (expertise of our project in the framework of a call for projects), we will perform a proof-of concept study to generate preliminary results for a future randomised placebo-controlled phase 3 study if the results are positive. Then, for the primary endpoint, the responder rate will not be compared to placebo, but assessed only for the donepezil arm after 16 weeks of treatment. Donepezil will be considered effective if 7 or more responders are observed in the 33 patients of the donepezil arm (see “statistics” paragraph for details). The responder rate will be compared to the placebo arm only for the secondary endpoint.

In the event of a beneficial therapeutic effect at the end of treatment (significant reduction in neuropathic disorders [reduction of one grade of neuropathy (according to NCI-CTCAE v4.0 or QLQ-CIPN20 score) or -30% of neuropathic pain (according to NRS 0–10 scale), if present, or PGIC score of 6 or 7]), the investigator will be allowed to request a lifting of the treatment blind, to adapt the further management of the patient and/or refer the patient to a specialist (neurologist, pain physician).

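### The success rule of 7 or more responders is defined only for 33 donepezil patients, but every completer out of 40 is analysed, so the rule will usually not match the analysed number

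*Protocol article*

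**What the plan says.** Under Sample size estimation, the article adopts a one-stage single-arm rule: "Fleming’s one-stage design will be used for sample size estimation". The null is a responder rate of 10%, and it "will be assessed against a one-sided alternative for the donepezil arm". The target is "Sixty-six evaluable patients (33 by arm) will be accrued", and the rule is "The null hypothesis will be rejected if 7 assessable or more responders are observed in the 33 patients of the donepezil arm". The stated properties are a type I error of 0.0417 and "a power of 91% for a responder rate of at least 30% in the donepezil arm". The section then raises enrolment to 40 per arm to cover 20% loss to follow-up and possible tumour recurrence.

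The section on the primary endpoint repeats the criterion: "Donepezil will be considered effective if 7 or more responders are observed in the 33 patients of the donepezil arm". Study design confirms the total: "The plan is to include 80 patients from 26 cancer centres and hospitals in France".

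Under Statistical analysis, the primary population is the per-protocol set, meaning patients who received the full 16 weeks of treatment at either dose. A one-sided 95% confidence interval for the responder rate is also planned. Its method is not named, and it is not linked to the decision.

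**The concern.** The rule and the population do not share a denominator. The rule speaks of 33 patients. The population is whoever completes out of 40, so its size is random. The article neither limits the analysis to 33, nor says which 33 would count, nor gives a cut-off for another number.

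Two things could follow. The analyst may apply 7, the only count stated, to a larger group; the quoted error rate then no longer holds. Or the cut-off may be chosen, or completers set aside, once the number is known. Either would weaken the decision that the article uses to judge donepezil effective and to justify a phase 3 trial.

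**Working it through.** **Inputs** (Sample size estimation, unless noted): null rate p0 = 10%; alternative p1 = 30%; one-sided test in the donepezil arm; cut-off 7 at n = 33; 40 patients randomised per arm; 20% loss. From Statistical analysis: all completers analysed, and a one-sided 95% interval, which implies a 5% one-sided benchmark.

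**Step 1: reproduce the stated figures.** With X ~ Binomial(n, p):
- Type I error = P(X ≥ 7 | n = 33, p = 0.10) = 0.0417.
- Power = P(X ≥ 7 | n = 33, p = 0.30) = 0.906, i.e. 91%.

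Both agree with the article. The design is correct at n = 33.

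**Step 2: how often is n equal to 33?** The expected number is 40 × 0.8 = 32. If losses are independent at 20% (an assumption), N ~ Binomial(40, 0.8):
- P(N = 33) = C(40,33) × 0.8^33 × 0.2^7 ≈ 0.15.
- P(N ≥ 35) ≈ 0.16.

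**Step 3: carry the count of 7 to other n.** The error is P(X ≥ 7 | n, 0.10). The exact (Clopper-Pearson) one-sided 95% lower limit for 7/n is the 5% quantile of Beta(7, n − 6).

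| n | Type I error with cut-off 7 | Lower limit for 7/n |
|---|---|---|
| 33 | 0.0417 | 10.4% |
| 34 | 0.0481 | 10.1% |
| 35 | 0.0552 | 9.8% |
| 36 | 0.0628 | 9.5% |
| 38 | 0.0800 | 9.0% |
| 40 | 0.0995 | 8.5% |

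The error passes the stated 0.0417 at n = 34 and passes 5% at n = 35. From n = 35, seven responders would meet the count while the exact interval still includes 10%.

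**Step 4: average over the evaluable number.** Averaged error = Σ P(N = k) × P(X ≥ 7 | k, 0.10), again with independent losses:

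| Loss | P(N ≥ 35) | Averaged error |
|---|---|---|
| 20% | 0.16 | 0.038 |
| 17.5% | 0.28 | 0.043 |
| 15% | 0.43 | 0.050 |
| 10% | 0.79 | 0.064 |

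**Step 5: cut-offs that hold the level.** The smallest r with P(X ≥ r | n, 0.10) ≤ 0.05 is 6 for n = 21–27, 7 for n = 28–34 and 8 for n = 35–41. These are also the smallest counts whose exact lower limit exceeds 10%. With cut-off 8:

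| n | Type I error | Power at 30% |
|---|---|---|
| 35 | 0.0200 | 86.7% |
| 36 | 0.0235 | 88.8% |
| 37 | 0.0274 | 90.5% |
| 38 | 0.0318 | 92.1% |
| 39 | 0.0366 | 93.4% |
| 40 | 0.0419 | 94.5% |

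**The case against.** A reader might infer that the plan fixes 7 for any number of patients and so runs a type I error of up to 10%. The article does not say that. Both statements of the rule tie 7 to 33, and the inflation arises only if someone carries the count over. That objection stands, and the error figures above are conditional on it.

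The planned attrition also tempers the size. At 20% loss the expected number is 32, where cut-off 7 gives an error of 0.036, and the average over N is about 0.038, below both 0.0417 and 5%. The 10% figure needs every donepezil patient to complete 16 weeks. This stands too, although the 20% is taken from practice with Alzheimer patients, a different population from these cancer survivors.

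The one-sided 95% interval is a partial safeguard, since an exact interval is valid at any n. It narrows the gap but does not close it: the article names neither its method nor its role in the decision.

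Finally, an unseen analysis plan or full protocol might adapt the cut-off, and a positive result only leads to a placebo-controlled trial. Leaving a detail to another document would be no finding. Here, however, the published rule and the published population disagree on the denominator of the primary decision.

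**Conclusion.** The point holds as a mismatch between the stated decision rule and the stated primary population. The 7-of-33 design is itself correct. The rule covers one denominator, which would occur about 15% of the time under independent 20% losses.

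If 7 is applied to a larger group, the one-sided error is 0.048 at 34 patients, 0.055 at 35, 0.063 at 36 and 0.0995 at 40, and from 35 the count can contradict the exact form of the trial's own interval. On average the error stays below 5% unless losses fall below about 15%; at 10% loss it is about 0.064. The documents therefore do not support a claim that the trial as planned has an inflated error, only that its rule is undefined at most attainable numbers and would be too lenient if used unchanged at 35 or more.

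The results rest on exact binomial tails, a 10% null and, for the averages, independent losses.

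**What to change.** In the primary endpoint section and in Sample size estimation, define success for the number actually analysed: the exact (Clopper-Pearson) one-sided 95% lower limit for the responder rate exceeds 10%. Give the equivalent cut-offs beside it: at least 6 responders for 21–27 patients, 7 for 28–34, 8 for 35–41. Keep 7 of 33 as the planned example. In Statistical analysis, name this interval as the decision criterion. Settle this before results are known.

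The cost is one short table and a sentence, with no further patients or data. The downside is some power where the cut-off steps up to 8: at a 30% responder rate it is 86.7% with 35 patients and 88.8% with 36, slightly under the stated 91%, and about 90.5% or more from 37 to 40.

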**Methods:**

The DONEPEZOX trial will be a proof-of-concept, randomised, triple-blinded, and multicentre study. It will be the first clinical trial evaluating the efficacy and safety of donepezil for the management of OIPN. Adult cancer survivors with OIPN that report sensory neuropathy according to QLQ-CIPN20 sensory score (equivalence of a grade ≥ 2), at least 6 months after the end of an oxaliplatin-based chemotherapy will be included. Eighty patients will be randomly assigned to receive either donepezil or placebo over 16 weeks of treatment. The primary endpoint will be the rate of responders (neuropathic grade decreases according to the QLQ-CIPN20 sensory score) in the donepezil arm. The severity of OIPN will be assessed by the QLQ-CIPN20 sensory scale before and after 16 weeks of treatment. The comparison versus the placebo arm will be a secondary objective. The other secondary endpoints will be tolerance to donepezil, the severity and features of OIPN in each arm before and after treatment, related-comorbidities and quality of life. Fleming’s one-stage design will be used for sample size estimation. This design yields a type I error rate of 0.0417 and power of 91% for a responder rate of at least 30% in donepezil arm. A total of 80 randomized patients is planned.

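### Eighty patients fall one short of 33 evaluable per arm at the plan's own 20% loss, so power is about 89% rather than 91% before any tumour recurrence

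*Protocol article*

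**What the plan says.** Under Sample size estimation, the protocol article sets up a one-stage Fleming design for the donepezil arm alone. The null value is given by "The null hypothesis that the responder rate is 10" per cent, which "will be assessed against a one-sided alternative for the donepezil arm". The requirement is "Sixty-six evaluable patients (33 by arm) will be accrued", and the null is rejected at 7 or more responders among the 33 donepezil patients. The type I error is stated in the words "This design yields a type I error rate of 0.0417"; power is put at 91% when the true donepezil response is 30% or higher.

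The recruitment target follows: "we have decided to include a total of 80 patients (2 × 40) to take into account lost to follow-up (20" per cent. That 20% is attributed mainly to poor tolerance at the starting dose or at the dose increase. The sentence then adds possible tumour recurrence to what the margin must cover, without a rate.

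Under Statistical analysis, the primary endpoint is analysed only in patients who received the full 16 weeks of treatment. The Abstract (Methods) repeats "This design yields a type I error rate of 0.0417 and power of 91" per cent beside the total of 80 and does not mention the 33 evaluable patients on which those figures depend.

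**The concern.** Three numbers in one paragraph do not agree: 33 evaluable per arm, 40 randomised per arm, and 20% loss. Because the primary population is completers, patients who stop for poor tolerance leave the primary analysis, so the loss comes straight off the denominator of the primary test. The placebo arm cannot compensate, since the test uses the donepezil arm only.

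What is at stake is the accuracy of the stated power. A reader who takes 80 patients, 20% loss and 91% power together is given a combination that the plan's own assumptions do not produce.

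**Working it through.** **Inputs (all from Sample size estimation unless noted).** Null rate 10%; alternative 30%; one-sided test in the donepezil arm; cut-off 7 responders; 33 evaluable per arm; 40 randomised per arm; 20% loss; completers-only primary population (Statistical analysis).

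**Formula.** For n evaluable patients and cut-off 7, the rejection probability at responder rate p is P(X ≥ 7) = 1 − Σ C(n,k) p^k (1−p)^(n−k), summed over k = 0 to 6. Type I error takes p = 0.10 and power takes p = 0.30.

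**Step 1: reproduce the plan's figures.** At n = 33, type I error is 0.0417 and power is 0.9056, which rounds to 91%. Both match the article.

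**Step 2: check the inflation.**
- Expected evaluable from 40 per arm: 40 × (1 − 0.20) = 32; in total 80 × 0.80 = 64, against 66 required.
- Number needed per arm: 33/(1 − 0.20) = 41.25, rounded up to 42 (84 in total).
- Largest loss that 40 per arm can absorb: (40 − 33)/40 = 17.5%.
- The total of 80 is what multiplication gives: 66 × 1.20 = 79.2, rounded up to 80. That this was the route taken is an inference; the article does not show the step.

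**Step 3: the same rule at the expected number.** At n = 32 with cut-off 7, type I error is 0.0358 and power is 0.8869. Against n = 33, power falls by 90.6 − 88.7 = 1.9 points (2.3 against the rounded 91%).

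**Step 4: allow the loss to vary.** If each of 40 patients independently has a 20% chance of loss, the chance of at least 33 evaluable is 44%. Power averaged over that loss, with the cut-off held at 7, is P(X ≥ 7 | 40, 0.30 × 0.80 = 0.24) = 87.7%.

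**Step 5: recurrence.** No rate is given, so the extra loss below is an assumption, shown as a range and added to the 20%.

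| Assumed extra loss | Evaluable per arm | Power, cut-off 7 |
|---|---|---|
| 0% | 32 | 88.7% |
| 2.5% | 31 | 86.5% |
| 5% | 30 | 84.0% |
| 10% | 28 | 78.0% |

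**The case against.** The strongest reply is that this amounts to one patient. At the only loss rate the article quantifies, power drops by about 2 points and type I error falls, so there is no false-positive cost. The trial is a proof of concept, and a positive result leads to a phase 3 study, so 89% instead of 91% would not change how it is read. All of that stands, and it limits the weight of the point. It does not make the figures consistent: the allowance for 20% is short before recurrence is counted at all.

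A second reply is that 0.0417 and 91% are attached to the rule at 33 evaluable patients, and are right there. That also stands. A reader might infer that the power calculation is wrong; it is not. The error lies only in the step from 66 to 80.

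A reader might also infer that the trial is seriously underpowered because of recurrence. The documents do not support a specific figure. Ongoing cancer is an exclusion, chemotherapy must have ended at least 6 months earlier, treatment lasts 16 weeks, and no recurrence rate is stated. The sentence can even be read as one loose allowance for both causes. The direction is clear; the size is unknown, which is why only a range is shown.

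**Conclusion.** The inconsistency is real and modest. At the plan's own 20% loss, the expected donepezil arm is 32 completers rather than 33, with type I error 0.036 and power 88.7% under the 7-responder rule. Power of 91% requires total loss of at most 17.5%. Any recurrence lowers power further, to between 86.5% and 78.0% over assumed extra losses of 2.5% to 10%.

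The conclusion rests on three things: a 30% responder rate among completers, the cut-off staying at 7 when fewer than 33 are evaluable, and removal of those who stop treatment from the primary analysis. The third is stated in the article. Type I error is not inflated by the shortfall.

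**What to change.** Keep 80 patients and correct the statement in Sample size estimation and in the Abstract. Suggested content: with 40 randomised per arm and 20% loss, 32 evaluable patients per arm are expected; the rule of at least 7 responders then has type I error 0.036 and power of about 89% at a 30% responder rate; the figures 0.0417 and 91% apply to 33 evaluable patients, that is, a total loss of at most 17.5%. For recurrence, give either a rate with its basis or the range 86.5% (31 evaluable), 84.0% (30) and 78.0% (28), labelled as assumptions. This costs wording only, and the stated power becomes slightly less favourable.

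If 33 evaluable at 20% loss is to be kept as the target, the alternative is 84 patients (2 × 42), plus any recurrence allowance. That means at least four more patients.

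Moving to an analysis of all 40 randomised donepezil patients with a cut-off of 8 is not a remedy. Its power of 94.5% assumes a 30% response among everyone randomised. If the 20% lost count as non-responders, the rate is 0.30 × 0.80 = 24% and power is about 78%, below the 88.7% it would replace.

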#### Statistical analysis

All statistical analyses will be performed using SAS software version 9.4 before breaking the randomization codes, according to International Conference on Harmonization-Good Clinical Practice guidelines. A two-sided *p*-value of less than 0.05 will be considered for the statistical significance of all the analyses. The results will be expressed as hazard-ratios and 95% confidence intervals. Secondary analyses will be exploratory.

The baseline description of the patients included in the analysis will be carried out, without presenting inferential statistical tests (according to recommendations). As part of a proof-of-concept, only patients who have completed the study (treatment received in its entirety for 16 weeks whatever the dose = per protocol population) will be analyzed for the primary endpoint. The primary endpoint will be the rate of responders and will be described using frequency and percentage. A 95% one-sided confidence interval will also be calculated. Subgroup analyses for the primary endpoint will be planned for each stratum of the randomization (neuropathy grade, age of neuropathy and type of chemotherapy).

For the secondary endpoints, analyses will be performed on the intention-to-treat and per-protocol populations and compared to the placebo arm.

Descriptive statistics will be presented by treatment arms. Continuous variables will be presented as mean and standard deviation (otherwise as median and interquartile range) and will be compared between arms using the unpaired t test or the Mann–Whitney U test when appropriate according to the assumptions of the t-test: (i) the Shapiro–Wilk test will be used to assess normality, and (ii) the Fisher-Snedecor test to assess homoscedasticity. When appropriate (for example, for the sensory scores of the QLQ-CIPN20), these analyses will be supplemented by the recommendations proposed by Vickers and Altman, i.e. ANCOVA, considering baseline scores as covariates. Then, multiple linear mixed models could be run with centers as random-effects. Covariates will be determined according to univariate results and to their clinical relevance, including stratification parameters. The normality of residuals will be studied as described previously. If appropriate, a transformation (for example logarithmic) should be proposed to achieve the normality of dependent variable. The results will be expressed as regression coefficients and 95% confidence intervals. The analyses of other continuous secondary endpoints (11-point pain NRS, DN4 interview, NPSI, HADS and QLQ-C30 questionnaires) will be carried out similarly. For categorical parameters (adverse effects, PGIC, DN4 interview or HADS categorized according to literature), Chi-squared or Fischer exact tests will be used to compare the treatment arms. A generalized linear mixed model (more precisely logistic regression for dichotomous outcomes) will be applied for multivariable analyses. The results will be expressed as relative risks and 95% confidence intervals.

Repeated data collected longitudinally will be analyzed by mixed models (linear or generalized linear according to dependent variable) to study the following fixed effects, arm, time and their interaction taking into account between and within patient variability (patient as random-effect, in addition to center effect) [62]. Particular attention will be paid to safety analysis (by group: type, intensity, frequency of adverse effects). Exit rates due to adverse effects will be considered as a censored data. These criteria will be estimated by the Kaplan–Meier method, compared between groups by the log-rank test, and investigated in a multivariate marginal Cox model considering center effects. The proportional-hazard hypothesis will be verified using Schoenfeld’s test and plotting residuals. Finally, to put significant results in perspective, a sensitivity analysis will be conducted to measure the impact of the missing data. A worst-case scenario will be defined as one where patients with missing data do not react to the treatment (whatever the treatment may be). Additional analyses will then be performed according to the statistical nature of missing data (missing at random or not), in particular multiple imputation or estimations proposed by Verbeke and Molenberghs [63] adapted specifically to repeated data.

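### The two-sided 0.05 level set for every analysis contradicts the one-sided primary test; the 7-of-33 count rule still governs at 33 evaluable patients, but at other numbers the only general level stated is the wrong one

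*Protocol article*

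**What the plan says.** In the protocol article, Sample size estimation uses a Fleming one-stage design for the donepezil arm alone. The null responder rate is 10%, and it "will be assessed against a one-sided alternative for the donepezil arm". The decision is a count: "The null hypothesis will be rejected if 7 assessable or more responders are observed in the 33 patients of the donepezil arm". The type I error is given as 0.0417 and the power as 91% at a true rate of 30%. The primary endpoint section repeats the rule: "Donepezil will be considered effective if 7 or more responders are observed in the 33 patients of the donepezil arm".

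The Statistical analysis section then opens with general sentences. One sets the significance level: "A two-sided *p*-value of less than 0.05 will be considered for the statistical significance of all the analyses". The next sets the effect measure: "The results will be expressed as hazard-ratios and 95% confidence intervals". Further on, the same section restricts the primary analysis to patients who completed 16 weeks of treatment, reports the primary endpoint as a frequency and percentage, and adds: "A 95% one-sided confidence interval will also be calculated".

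**The concern.** Two explicit statements about the same test disagree. Sample size estimation makes the primary test one-sided; the general sentence, read literally, makes it two-sided at 0.05. The one-sided interval in the analysis section fits the first and not the second, so that section contains both conventions.

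The primary result decides whether donepezil is taken to a placebo-controlled phase 3 trial, so the level for that decision should not be open to choice once the data are in. The stated 91% power also belongs to the one-sided rule only. The count rule protects the decision when exactly 33 patients are evaluable. Forty are to be randomised to donepezil and only completers enter the primary analysis, so another number is quite possible. An analyst would then need a significance level, and the only general one stated is two-sided.

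**Working it through.** **Inputs.** From Sample size estimation: null rate 10%, alternative 30%, 33 evaluable donepezil patients, success at 7 or more, 40 randomised per arm, 20% expected loss. From Statistical analysis: two-sided 0.05 for all analyses, one-sided 95% interval for the primary endpoint, completers only.

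**1. The plan's own figures.** Let X be the number of responders among 33.
- Type I error: P(X ≥ 7 | 33, 0.10) = 0.0417.
- Power: P(X ≥ 7 | 33, 0.30) = 0.906, that is, 91%.

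Both agree with the article, which confirms that the design is an exact one-sided test.

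**2. The boundary result 7/33 = 21.2%, one-sided.** Exact p = 0.0417. The Clopper-Pearson one-sided 95% lower bound is the 5% point of a Beta(7, 27) distribution, 10.4%, which lies above 10%. Rule, p-value and interval agree.

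**3. The same result read two-sided.** The article names no two-sided one-sample method, so several were tried:

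| Two-sided method at 7/33 | Result | Rejects 10%? |
|---|---|---|
| Doubled exact tail, 2 × 0.0417 | p = 0.083 | no |
| Clopper-Pearson 95% interval | 9.0% to 38.9% | no |
| Doubled mid-p | p = 0.056 | no |
| Score, continuity-corrected | p = 0.063 | no |
| Wald | p = 0.115 | no |
| Minimum-likelihood exact | p = 0.0417 | yes |
| Score, uncorrected | p = 0.032 | yes |
| Wilson 95% interval | 10.7% to 37.8% | yes |

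The minimum-likelihood test adds nothing from the lower tail, because P(X = 0) = 0.0309 exceeds P(X = 7) = 0.0276. Its p-value therefore equals the one-sided one.

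**4. Cost of an equal-tail reading at 33.** With 0.025 in the upper tail the cut-off becomes 8: P(X ≥ 8 | 33, 0.10) = 0.0141 and P(X ≥ 8 | 33, 0.30) = 0.818. The power lost is 0.906 − 0.818 = 0.088, which is also the chance of exactly 7 responders at a true rate of 30%.

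**5. Evaluable numbers other than 33.** Applying the 20% loss to one arm gives 40 × 0.80 = 32, so 33 is not a certain figure; the ceiling is 40. The range 30 to 40 is my assumption. For each n, the smallest count with upper-tail probability under 10% of at most 0.05 or at most 0.025 (attained level in brackets) is:

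| n | One-sided 0.05 | 0.025 per tail |
|---|---|---|
| 30 | 7 (0.0258) | 8 (0.0078) |
| 31 | 7 (0.0306) | 8 (0.0096) |
| 32 | 7 (0.0358) | 8 (0.0117) |
| 33 | 7 (0.0417) | 8 (0.0141) |
| 34 | 7 (0.0481) | 8 (0.0169) |
| 35 | 8 (0.0200) | 8 (0.0200) |
| 36 | 8 (0.0235) | 8 (0.0235) |
| 37 | 8 (0.0274) | 9 (0.0093) |
| 38 | 8 (0.0318) | 9 (0.0111) |
| 39 | 8 (0.0366) | 9 (0.0131) |
| 40 | 8 (0.0419) | 9 (0.0155) |

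The cut-offs differ by one responder at 9 of 11 sizes and agree at 35 and 36. At 32 the power at a true 30% is 0.887 against 0.788; at 40 it is 0.945 against 0.889.

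**The case against.** The strongest reply is that the primary decision is a count, not a p-value. It is stated in matching terms in two sections, its error rates reproduce, and the analysis section gives the primary endpoint a percentage and a one-sided interval but no two-sided test. On ordinary reading the specific rule overrides a generic opening sentence, and seven responders in 33 is a success. That stands.

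It also answers three stronger readings that a reader might infer:
- **That 7/33 flatly succeeds one-sided and fails two-sided.** The documents do not support this. No two-sided method is named, and three of the methods tabulated above still reject.
- **That the unnamed interval method can overturn the result.** A Wald one-sided lower bound would be 0.2121 − 1.645 × √(0.2121 × 0.7879 / 33) = 9.5%, below 10%. But the interval only supplements the count rule and nowhere decides success, and its formula is a detail commonly left to the analysis plan.
- **That the primary endpoint is to be reported as a hazard ratio.** The article reports it as a frequency and percentage. It assigns regression coefficients to continuous outcomes, relative risks to categorical ones and a Cox model to discontinuation. The hazard-ratio sentence is loose general wording.

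The reply does not cover an evaluable number other than 33, where the article has no count to fall back on. Nor does it remove the contradiction: the sentence says all analyses and exempts none.

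**Conclusion.** The contradiction is real but narrow. As written, the general sentence puts the primary test at two-sided 0.05, against the one-sided test in Sample size estimation and the one-sided interval in the same section. The design itself is sound: 7/33 is a success, and 0.0417 and 91% are right.

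The size depends on two assumptions. If two-sided is taken as equal-tail exact, 7/33 is no longer significant and the cut-off moves to 8, with power about 82%; under a minimum-likelihood exact test nothing changes at 33. If the evaluable number differs from 33, an equal-tail reading usually moves the cut-off by one responder relative to one-sided 0.05. The analysis plan, which is not shown, may settle the rule for other numbers, but it would then have to depart from the sentence in the article. The correction should be made before analysis, because it fixes in advance the level for the phase 3 decision and costs almost nothing.

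**What to change.** 1. State that the primary endpoint is tested by an exact one-sided binomial test of the donepezil responder rate against 10% at one-sided 0.05 (attained level 0.0417 at 33 evaluable patients). This also supplies a cut-off for any other evaluable number.
2. Name the Clopper-Pearson one-sided 95% lower bound as the accompanying interval, since it agrees with the count rule.
3. Limit the two-sided 0.05 sentence to the exploratory between-arm analyses.
4. As a minor wording correction, limit hazard ratios to the Cox model for treatment discontinuation.

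The cost is a few sentences in the statistical section. The 7-of-33 rule, sample size, type I error and power stay as stated.
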